##

### Full Study Title

Treatment of Personality Disorders Project - “Treatment of personality disorders using a whole of service guidelines-based approach to improve functioning and reduce hospital use: a delayed randomised controlled trial”

### Statement of Compliance

This document is a protocol for a clinical research study. The study will be conducted in compliance with all stipulations in this protocol and the NHMRC National Statement on Ethical Conduct in Human Research (2007).

### Ethical Considerations

The clinical research study involves the evaluation of a model of care for people with personality disorders in partnership of NSW Health. The intervention is conducted by employees of NSW Health, with the University developing the model of care.

The study will be approved by the institutional review board.

The Institutional Review Board considers these applications in two steps - Human Research Ethics Committee of the University of Wollongong approves the approach to the intervention, and the Health Service provides site specific approval for access to medical records. Patients provide approval for their health records to be used for service delivery and service improvement and research, and the provision of anonymous records to researchers protects their rights to privacy with adequate safeguards overseen by the joint University-Health Service Ethics Committee (IRB).

### Amendments to protocol

Amendments to the trial protocol will be recorded in the trial registration website.

# Protocol Synopsis

| Title | Treatment of personality disorders using a whole of service guidelines-based approach to improve functioning and reduce hospital use: a delayed randomised controlled trial |
| --- | --- |
| Objectives | The aim of this study is to evaluate the efficacy of a whole of service approach to treatment of personality disorder |
| Design | Delayed randomised controlled trial |
| Outcomes | The primary outcome is change in hospital use measured by audit of medical record admission and discharge data. Secondary patient outcomes will be measured. |
| Study Duration | The study duration is 3 years. |
| Interventions | There is an intervention and treatment as usual arm. The intervention is a whole of service guidelines-based approach |
| Number of Participants | The study is expected to target at least 70 people |
| Population | The population involves people with personality disorder who are clients of the health service |

# Investigators and Facilities

### Study Location/s

The study involves the following locations in Australia:

*Researcher Location:*

The researchers are based at the University of Wollongong.

*NSW Health Location:*

The intervention clinicians are in the South Eastern Sydney and Illawarra Health service. The two study locations are centred on the Shellharbour hospital precinct and surrounding mental health units and services, and the St George/Prince of Wales hospital precinct and surrounding mental health units and services. The two services are similar in catchment size, staffing and clinical flow through; but are separated by a national park and natural landforms ensuring they are also serving distinct populations with separate staff servicing each precinct. This minimises contamination between sites.

### Funding and Resources

This research is funded by NSW Health. The contract for the administration of the grant is through a partnership between the University of Wollongong and the Health Administration Corporation (HAC), NSW Health DOH09/33

# Introduction and Background

### Abbreviated Background

Personality disorder patients regularly present to emergency departments with self-harm or suicidal threats, and are often prematurely disengaged from treatment due to the perception that personality disorders are difficult to treat (Bateman, 2000). The clinical literature is also replete with examples of difficulties establishing rapport, high drop-out rates, and pervasive non­ compliance (McWilliams, 1994). The emotional demands on clinicians working with personality disorders are certainly well-recognised, with clinicians often reporting concern about working with this population (Brody & Farber, 1996). As a consequence, understanding and responding appropriately to personality disorder patients' needs with adequate treatment will be not only benefit personality disorder patients but may also enhance clinician competence and confidence and therefore better utilise current clinical services. Systematic investigation of current treatment programs for personality disorders will provide us with the information required to develop innovative, clinically applicable treatments for patients with personality disorders based on best research evidence. Developing our understanding of treatments will also enable clinicians to share this knowledge with patients, carers and families and will result in more collaborative and shared treatment experiences for this vulnerable population. An additional aim of the study is to distribute the knowledge acquired in the current study to mental health service systems state-wide and therefore work towards more efficacious treatments being widely available to personality disorder patients in the future. We will compare services with a specialised personality disorder service (using a stepped care model) to those without such a service across South Eastern and Illawarra Area Health Service.

### Research Question

Will a whole of service guidelines-based treatment approach be superior to treatment as usual (TAU)?

# Study Objectives

### Primary Objectives

The aim of this study is to evaluate the efficacy of a whole of service approach to personality disorders.

We will assess the impact of the implementation compared to TAU on a service level.

Clinical patients will therefore get the standard care offered in their service, however the care will vary between sites. One site will implement the intervention (whole of service approach), whereas the other will continue with standard treatment as usual.

We will study the impact of the intervention by using hospital records (inpatient admissions and emergency department presentations).

The study has two aims: (1) to assess the impact of the implementation compared to TAU on a service level, using hospital records (primary outcome), and (2) to assess the impact of the implementation on individual patient outcomes and therapist knowledge and attitudes (secondary outcomes).

# Study Design

### Type of Study

The study is a delayed randomised controlled trial. There are two treatment groups; intervention (whole of service approach) and TAU (treatment as usual) control. The study involves a baseline "treatment as usual" period for both groups, followed by one group adopting the whole of service intervention. The study is designed to determine potential superiority of the intervention over the TAU control group.

### Preliminary Study Design Diagram

**CONSORT Flow Diagram**

Randomized – 2 sites

Assessed for eligibility – 2 sites

18 month baseline

## Enrollment

Excluded (not meeting inclusion criteria)

## Allocation

Allocated to TAU – site 2

Received TAU at control site

Did not receive allocated control

Allocated to intervention – site 1

Received allocated intervention

Did not receive allocated intervention

Lost to follow-up

Lost to follow-up

Analysed
♦ Excluded from analysis

## Follow-Up

## Analysis

Analysed
♦ Excluded from analysis

### Number of Participants

It is expected that at least 70 participants will be involved in the study (35 in the intervention group and 35 in TAU control).

### Expected Duration of Study

The three year study will be in two 18 month periods - and 18 month baseline recruitment and an 18 month active intervention followup period.

### Primary Outcomes

11.1 Primary Outcome

The primary outcome involves the change in hospital use measured by audit of medical record admission and discharge data. Specifically, number of presentations to the inpatient unit, number of bed days in the inpatient unit, and number of presentations to the emergency department. Secondary analyses will involve ratings of severity of diagnostic symptoms and changes in staff confidence and skills.

# Study Treatments

### Treatment Arms

- 1. The Intervention Group

All participants attending the intervention study site for personality disorder treatment will receive the whole of service intervention. This will involve implementing a stepped care model whereby brief intervention psychological clinics are established. The role of the brief intervention clinic (Gold Card Clinic) is to transition patients with personality disorder who present in crisis for clinical services to:

(a) emergency,

(b) inpatient, or

(c) acute care services (including through the telephone triage service)

These patients will be referred, within 0-36 hours, to the brief intervention clinic attached to their acute care team for psychological therapy.

The Gold Card Clinic is a brief intervention service for people in the catchment area who have recently experienced a mental health crisis involving a diagnosed personality disorder (including self-harm and/or suicidal thoughts or behaviours).

It is one part of a whole of service stepped care approach. The goals of the stepped care model is to ensure the best and most timely use of resources based on the individual needs of the patient and their families/carers.

The GCC aims to offer an appointment within 1-3 working days of referral and offers an initial 3 sessions that focus upon identifying and addressing psychological and lifestyle factors that contributed to the crisis. An additional session for carers, partners and family members is included in the intervention.

The key aims of this intervention are to:

• provide a timely and rapid response to people seeking treatment in crisis

• provide an alternative to hospitalisation or facilitate early discharge

• provide brief interventions to help manage the client’s immediate needs

• provide brief clinical services aimed at helping the client solve their problems

• provide assessment and psycho-education to help the client understand their problems

• provide tools and strategies to help the client prevent and better manage future crises

• provide an opportunity to assess the client’s needs, including the possible need for other services where necessary

• provide an opportunity to connect with the person’s family, partner or carer where desirable

• provide treatments with an evidence-base that are effective with personality disorders

The GCC will operate during the usual opening hours of community health services (Monday-Friday, 0830-1700) and will not be available to receive referrals or meet with consumers or carers on weekends or public holidays.

Referrals

Referrals to the Clinic can be made by a range of services, including:

• Emergency Department (ED)

• Psychiatric Emergency Care Centre (PECC)

• Mental Health Intensive Care Unit (MHICU)

• Community Mental Health Team

• Community Rehabilitation Team

• Aboriginal Community Health Centre

• Early Psychosis Program (EPP)

• Acute Care Team (ACT)

Referral to crisis services

If the GCC Clinician assesses at any time that the level of risk requires an extremely urgent response they should always contact the emergency services immediately.

If the level of risk appears to require a response of any other level of urgency (i.e. low, medium or high urgency) the GCC Clinician should contact Central Intake to consider a referral to the ACT.

Discharge procedure

As a GCC Clinician is approaching the end of their work with a consumer they will bring the case to the GCC Review Meeting for discussion and discharge planning in consultation with the GCC Consultant Psychiatrist, who will ultimately authorise the person’s discharge from the service and where appropriate arrange a transfer of care to another mental health service.

As a central part of the discharge procedure the GCC Clinician will carry out a careful and collaborative consideration of further treatment and support options with the consumer and, where possible, with carers, family members and partners. This may involve a variety of actions, including but not limited to:

• Provision of resources and information about services and supports

• Signposting to specific resources, supports, services and local specialist clinicians

• Formal referrals to specific services and local specialist clinicians

• Liaison with identified local specialist clinicians to facilitate transition into longer-term treatments

• Liaison with GPs to facilitate arrangements for follow-up in primary care and access to ATAPS and Better Access Initiatives

- 1. The TAU Control

The control group involves treatment as usual (TAU) with the usual care provided by the health service for people with personality disorder seeking treatment.

# Participant Enrolment and Randomisation

### Recruitment

Participants will be clients of the health service with a diagnosis of personality disorder who have been admitted to the inpatient unit within the baseline 18 month study period.

### Inclusion Criteria

The inclusion criteria are clients having a primary diagnosis of ICD-10 personality disorder who are a mental health inpatient of the Health Service within the 18 month baseline recruitment period. They must be aged 12 or over.

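### The admission that makes a patient eligible is also counted in the baseline outcome, which builds in a fall at both sites; separately, a cohort of baseline inpatients cannot answer the service-level aim.

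*Protocol*

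**What the plan says.** Under Inclusion Criteria, eligible patients are those "who are a mental health inpatient of the Health Service within the 18 month baseline recruitment period". Recruitment says the same: participants are people "who have been admitted to the inpatient unit within the baseline 18 month study period". Expected Duration of Study makes recruitment and baseline one window: "18 month baseline recruitment and an 18 month active intervention followup period". The Table of Procedures Schedule marks recruitment in months 0-18 only, and marks monitoring of emergency use and bed days in both months 0-18 and months 19-36.

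Section 11.1 states: "The primary outcome involves the change in hospital use measured by audit of medical record admission and discharge data". The components are "number of presentations to the inpatient unit, number of bed days in the inpatient unit, and number of presentations to the emergency department". No section takes the qualifying admission out of the baseline count.

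On purpose, Primary Objectives says: "We will assess the impact of the implementation compared to TAU on a service level", and ties this first aim to the primary outcome. On who is treated, Treatment Arms says: "All participants attending the intervention study site for personality disorder treatment will receive the whole of service intervention". The clinic takes people in crisis from emergency, inpatient and acute care, including telephone triage.

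On analysis, the Statistical Analysis Plan section directs attention to the time by site interaction in a mixed model. One site is allocated to each arm.

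**The concern.** There are two separate problems.

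The first is selection on the outcome. Every participant has at least one baseline admission, with its bed days, because that is how they entered. Nothing requires one in follow-up. The baseline count is cut off at one or more and the follow-up count is not, so the mean change is negative even if nothing was done. A fall within the intervention site therefore says nothing about the intervention. The between-site contrast is safe only if the built-in fall is equally large at both sites.

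The second is the population. The cohort closes at the end of baseline. Someone first admitted in months 19-36, or who only ever attends emergency, never enters. A first admission that the clinic prevents cannot be seen, and neither can beds taken up by new patients. The first aim is then answered only for people who had already been inpatients. This would be so even if there were no regression to the mean.

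**Working it through.** The protocol states no admission rate, variance or effect size, and its figure of at least 70 participants (35 per group) is an expected count, so there is no plan figure to reproduce. The rates below are assumptions.

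**Model.** Each person has a constant admission rate. Across the unselected population the rate is gamma with mean m per 18 months and shape k. Counts in the two windows are Poisson given the rate, the windows are equally long, and there is no treatment effect.

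**Formulas.**
- Chance of no baseline admission: p0 = (k/(k+m))^k.
- Baseline mean among those selected: m/(1-p0).
- Follow-up mean among those selected: m × [1-(k/(k+m))^(k+1)]/(1-p0).
- Proportional fall, from the ratio of the two: (k/(k+m))^(k+1).

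**Step 1: the fall at one site.**

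| m | k | p0 | Baseline | Follow-up | Change | Fall |
|---|---|---|---|---|---|---|
| 0.3 | 0.5 | (0.5/0.8)^0.5 = 0.791 | 0.3/0.209 = 1.43 | 0.72 | -0.71 | 49% |
| 0.5 | 0.5 | (0.5/1.0)^0.5 = 0.707 | 0.5/0.293 = 1.71 | 1.10 | -0.60 | 35% |
| 0.6 | 0.5 | (0.5/1.1)^0.5 = 0.674 | 0.6/0.326 = 1.84 | 1.28 | -0.56 | 31% |
| 1 | 1 | (1/2)^1 = 0.500 | 1/0.5 = 2.00 | 1.50 | -0.50 | 25% |

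Over shapes 0.3 to 1.0 and means 0.2 to 1.0, the smallest fall is at k = 0.3, m = 1: (0.3/1.3)^1.3 = 15%. The largest is at k = 1, m = 0.2: (1/1.2)^2 = 69%. At higher rates it shrinks: at m = 4 it is 2% to 4% for shapes from 0.25 upwards.

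**Step 2: a within-site test.** With 35 patients and m = 1, k = 1, a pre-post t test at 5% rejects in 43% of simulated trials with no effect.

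**Step 3: the planned contrast, sites alike.** With two windows, the time by site interaction is the difference between the sites in mean change. If m and k are the same at both sites, its expected value is 0. With m = 1, k = 1, simulation gives rejection of 5.0% at 35 per site and 5.1% at 300. The artefact cancels.

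**Step 4: the planned contrast, sites different (k = 0.5 at both).**
- Means 0.3 and 0.6: -0.708 - (-0.564) = -0.14 admissions per patient.
- Means 0.5 and 0.6: -0.604 - (-0.564) = -0.04.

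Simulated rejection with no effect, by a two-sample t test on change scores at 5%:

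| Site means | 35 per arm | 100 per arm | 300 per arm |
|---|---|---|---|
| 0.3 and 0.6 | about 7% | about 12% | about 26% |
| 0.5 and 0.6 | about 5% | about 5% | about 7% |

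A more extreme pair, 0.5 and 2 with k = 1, gives -0.33 admissions and rejection of 12% at 35 and 61% at 300. The number per arm matters because the Sample Size section takes every eligible inpatient, so 70 is a floor.

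**Step 5: who is counted.** Set Recruitment beside Treatment Arms. Entry needs an inpatient stay in months 0-18, whereas treatment goes to anyone in crisis at the intervention site. People who first present in months 19-36 are in the second group and never in the first. No arithmetic is needed here.

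**The case against.** The strongest answer is that the protocol never plans to read the within-arm fall as an effect. Its contrast is the interaction against a concurrent control site, selected by the same rule over the same windows, and Step 3 shows that this removes a common fall. That stands. The 15% to 69% is not bias in the planned estimate.

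A reader might infer that the sites must differ in admission thresholds and that the interaction is therefore biased. The documents do not support this. Study Location/s describes the two services as comparable in size, staffing and patient flow, and for modest differences the inflation is negligible at 35 per arm. What remains is narrower. That section is silent on admission rates among people with personality disorder, it says the populations are distinct, and with a single site in each arm randomisation cannot make them match.

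A reader might also infer that regression to the mean is why the service-level aim goes unanswered. It is not; the closed cohort is.

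Finally, a cohort fixed before the intervention starts has a real merit: the intervention cannot alter who belongs to it. An open comparison loses this, because a new clinic could change who is diagnosed or coded at one site. That is a good reason to keep the cohort analysis and not replace it.

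**Conclusion.** The concern holds in two limited parts.

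1. Counting the qualifying admission in baseline builds in a fall at each site. Any bias in the planned interaction depends on whether the sites' admission-rate distributions differ. If they do not, there is none. For a twofold difference in the assumed mean (0.3 and 0.6) it is about -0.14 admissions per patient, with rejection of about 7% at 35 per arm and 26% at 300. For 0.5 and 0.6, rejection is about 5% to 7%. These figures rest on constant individual rates, equal windows and assumed means and shapes. They cover admissions only; bed days and emergency presentations were not modelled.

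2. The cohort as defined cannot answer the first aim at service level. This rests on the text alone.

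The documents do not support the claim that the planned comparison is invalid or that its result is certain to be biased. Both parts are nevertheless worth correcting, because the protocol itself sets the eligibility rule, the recruitment window and the outcome.

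**What to change.** 1. In the cohort analysis, remove the qualifying admission from the baseline counts, with its bed days and any linked emergency presentation. Start baseline time at discharge from that stay. Use a count model with a person-time offset and compare rates within person. Under the model above, admissions after the qualifying one still occur at the person's own rate, so the within-person comparison has no built-in fall. A pooled rate would not be enough, because people with higher rates tend to qualify earlier and contribute more baseline time.
2. State that within-arm change will not be interpreted as an effect of the intervention.
3. For the first aim, add an open site-level comparison: monthly emergency and inpatient rates with a primary personality disorder diagnosis, at each site, in both windows. The alternative is to restrict the conclusion to people who were inpatients at baseline.

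**Cost.** No new type of data is needed, since Data Collection already describes extracting emergency and inpatient records with that diagnosis. The cohort loses some baseline person-time and precision. The open comparison may be affected by changes in diagnosis or coding at the intervention site, does not cover acute-care or telephone-triage contacts, and still has one site per arm.

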### Randomisation Procedures

The study will use a computer generated randomisation sequence to allocate study sites to intervention or control. The randomisation will be performed independently from the health service and the sites.

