### Statistical Analysis Plan

The statistical analysis plan is to evaluate the use of health care resources across the study sites with particular attention on time x intervention site interactions. The general linear model will be employed, specifically a mixed models analysis, with the covariance structure for residuals specified as ante-dependent (first order).

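### With two sites randomised, one per arm, the intervention cannot be separated from site-specific change after baseline, so the design does not support the planned superiority conclusion

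*Protocol*

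**What the plan says.** Section 15 of the protocol (Randomisation Procedures) states: "The study will use a computer generated randomisation sequence to allocate study sites to intervention or control". The flow diagram in section 8 gives the number of units, "Randomized – 2 sites", and places one in each arm: "Allocated to intervention – site 1" and "Allocated to TAU – site 2". Section 6 (Primary Objectives) says the same in words: "One site will implement the intervention (whole of service approach), whereas the other will continue with standard treatment as usual".

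Section 7 labels and aims the study: "The study is a delayed randomised controlled trial", and "The study is designed to determine potential superiority of the intervention over the TAU control group". The synopsis and section 6 state the aim as evaluating efficacy, and section 5 poses the research question as one of superiority.

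Section 21 evaluates health care use "with particular attention on time x intervention site interactions", in a mixed model with a first-order ante-dependence structure for the residuals. It names no site-by-period component.

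Section 9 expects at least 70 patients, 35 per arm. Section 20 takes every eligible inpatient from the baseline period.

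**The concern.** With one site per arm, treatment and post-baseline status at site 1 are the same variable. The time-by-site interaction estimates the intervention effect plus any difference in how the two sites changed for other reasons. The primary outcomes in section 11 are inpatient presentations, bed days and emergency presentations. A change in bed numbers, staffing, admission policy or coding at one hospital could move them directly.

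The model takes its error from variation among patients within sites. Site-specific change therefore enters the estimate but not its standard error. More patients at the same two sites shrink the standard error and leave this component as it was. At stake is whether a small p-value for the interaction can be read as evidence that the intervention is superior, which is how the protocol frames it.

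This is not a detail that a separate SAP could settle. The number of randomised units and the claimed conclusion are fixed in the protocol, and no covariance structure or added random effect creates between-site replication.

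**Working it through.** **Inputs from the protocol.** Randomised units: 2 sites, 1 per arm (sections 6, 8, 15). Patients: 35 per arm, total at least 70 (section 9). Contrast: time by site (section 21). The 70 comes with no alpha, power, effect size or variance, so there is no calculation to reproduce.

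**Step 1: what randomisation supplies (no assumptions needed).** With k sites per arm there are C(2k, k) possible allocations, and the smallest two-sided randomisation p-value is 2 / C(2k, k). Between-site degrees of freedom are 2k − 2.

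- k = 1 (this trial): C(2, 1) = 2 allocations; smallest p = 1/2 = 0.5 one-sided and 2/2 = 1.0 two-sided; degrees of freedom = 2 − 2 = 0.
- For scale, the smallest two-sided p is 2/6 = 0.333 for k = 2, 2/20 = 0.10 for k = 3 and 2/70 = 0.029 for k = 4. A randomisation test could reach two-sided 0.05 only from four sites per arm.

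**Step 2: what the baseline removes.** Write the mean at site s in period t as a stable site level, plus a common period effect, plus a site-by-period deviation with variance τ², plus the intervention effect at site 1 in follow-up. In the difference between sites in their change, the site levels and the common period effect cancel. Four site-by-period deviations (2 sites × 2 periods) remain and contribute 4τ². With one site per arm τ² cannot be estimated.

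**Step 3: illustration of the effect on the nominal 5% test.** Assumptions, none of them in the protocol: patient variance 1, pre/post correlation ρ = 0.5, normal theory, and τ² of 1% or 2% of patient variance.

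- Variance used by a patient-level model: V₀ = 2 × 2(1 − ρ)/n = 4(1 − ρ)/n.
- Variance with the site-by-period component: V₁ = V₀ + 4τ².
- Actual type I error: 2 × [1 − Φ(1.96 / √(V₁/V₀))].

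| n per site | V₀ | τ² | V₁ | V₁/V₀ | Type I error |
|---|---|---|---|---|---|
| 35 | 0.0571 | 0.01 | 0.0971 | 1.70 | 13.3% |
| 35 | 0.0571 | 0.02 | 0.1371 | 2.40 | 20.6% |
| 100 | 0.0200 | 0.01 | 0.0600 | 3.00 | 25.8% |
| 100 | 0.0200 | 0.02 | 0.1000 | 5.00 | 38.1% |

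The 100-per-site rows are hypothetical. They show the direction if the open-ended intake exceeds the expected minimum.

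**Step 4: sensitivity.** At n = 35, moving ρ from 0.3 to 0.7 gives 11% to 18% for τ² = 0.01 and 17% to 28% for τ² = 0.02. The component can also be expressed as an intraclass correlation of the change score. A τ² of 0.01 with ρ = 0.5 then corresponds to 0.02/(1 + 0.02) ≈ 0.02. The design-effect formula at 0.02 gives 1 + 34 × 0.02 = 1.68 and a type I error of 13.0%, in agreement with the first row. If τ² = 0 the error is 5%.

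**The case against.** The two-site design is openly stated and reasoned. Section 1 describes the services as comparable in size, staffing and throughput, and as geographically separate to limit contamination. Allocation is by chance and done independently of the sites, which protects against choosing the site more likely to improve. Section 6 sets the aim at service level, and the planned inference is model-based with a long baseline.

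Much of this stands. A controlled before-after comparison of two services is a legitimate study, and the randomisation p-value describes a test that the protocol does not propose. But similarity at the outset does not prevent later divergence, and separation addresses contamination only. Separate staff and populations make independent drift more plausible, if anything. The model-based comparison needs the assumption of no differential drift, which the protocol does not state.

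It is also fair that the type I error figures depend on chosen variances and on normal theory for counts and bed days.

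Three stronger readings might be inferred, and the document does not support them:

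- *No inference is possible at all.* What is lacking is randomisation-based superiority. A contrast conditional on these two sites survives under parallel trends.
- *The word delayed is wrong because the control site never crosses over.* Section 7 explains the design as a usual-care baseline for both groups before one adopts the intervention, and section 18 schedules that. No crossover is promised.
- *The test is known to be badly inflated, all the more with several hundred patients per site.* The protocol gives no site-by-period variance and no basis for numbers of that order.

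**Conclusion.** The point holds in this form. Intervention and site-specific change after baseline are fully confounded, between-site degrees of freedom are zero, and the smallest two-sided randomisation p-value is 1.0. These three facts follow from the protocol alone. The efficacy and superiority conclusion in the synopsis and in sections 6 and 7 therefore claims a property that the design lacks.

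The statement that intervals are too narrow is conditional: it is true for a claim about the intervention if any site-by-period variance exists. The type I error of about 13% (21%) at 35 per site, and 26% (38%) at 100, is an illustration resting on the assumed variance, correlation and normal theory in the working. It is not an estimate for this trial.

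**What to change.** 1. In the synopsis, the objectives and sections 7, 15 and 21, describe the study as a two-site controlled before-after comparison with sites allocated by chance. Replace the efficacy and superiority conclusion with *difference in change between these two sites*. State that intervals are conditional on these sites and exclude between-site variation. State the parallel-trends (no differential drift) assumption on which a causal reading depends.

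2. As a supporting analysis, if the extracted records are dated, fit a controlled interrupted time series by site, allowing for season and autocorrelation, and report whether baseline trends are parallel. Use all personality disorder presentations and discharges in the section 22 extract, not only the trial cohort. That cohort is selected on an admission during baseline (sections 13 and 14), which distorts its baseline level and slope. State that the series does not create site replication, and that parallel baseline trends do not exclude a site-specific shock coinciding with rollout.

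The cost is a wording amendment, a modest further analysis of records already planned for extraction, and a weaker headline claim.
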